### Duration

Approximately 3000 EUS procedures are performed at CHUM annually, including approximately 300 adenocarcinomas of the pancreatic genu/body/tail, of which 90% (270) are inoperable and have pain. Given a sample size requirement of 90 patients and allowing for a 50% refusal/dropout rate, this study could be completed in approximately one and a half years. This was the approximate time frame for our previous RCT on neurolysis in the same patient population [4]. An extra 3 months will be necessary for completion of data analyses and drafting of the manuscript. The study will be terminated as soon as recruitment is complete. An extension will be requested if recruitment is not complete after one and a half years.

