### Sample size calculations

The sample size, estimated in relation to the primary outcome, is based on the detection of a minimum clinical difference of 3 points on the Likert scale between the 2 study groups, with a beta error of 20%, an alpha error of 5%, and a standard deviation of 7. *n* = 2 × 7.8 × (7/3) 2 = 2 × 7.8 × 5.4 = 90 per group.

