### Patient follow-up

Patients will be followed in the immediate post-procedural period until 4 months after the procedure or death whichever comes first; see Fig. 1.

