### Statistical analysis

Descriptive statistics will assess patient characteristics (demographics, tumor size) and the balancing of randomization. The data will be tested for normality, and the paired Wilcoxon ranked sum test will assess the pain scores. Student’s *t* test will be performed when comparing two means. Fisher’s exact method will be used for proportions comparison. All *p*-values are two-tailed, and values < 0.05 will be considered statistically significant. Subsequent logistic regression modeling will determine the factors that are associated with a better pain outcome.

Kaplan-Meier estimates of the survival curve will be obtained for each treatment group, and statistical comparisons of these will be performed using the log-rank test. The Cox proportional hazards models will be used to study survival while adjusting for potential confounding factors.

Patients who withdraw will be noted and will be noted and they will be excluded from analysis.

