## Trial status

The CRCHUM Research Ethics Board (REB), more precisely its CT2 Panel, has reviewed this research project at its full board meeting where quorum was reached. It was approved, with number of 2022-9969, 21.151. Approval was communicated to the principal investigator on September 21, 2021. No REB member withdrew from the deliberations. Any protocol modification will be submitted to the REB. We have started recruitment on November 2, 2021, and 36 patients have been recruited to date. The recruitment is expected to continue until the target sample size is reached.

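### The Duration section gives the requirement as 90 patients where the calculation gives 90 per group (180), and its study-end rule conflicts with the 4-month follow-up

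*Protocol article*

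**What the plan says.** **Sample size.** The Sample size calculations section plans for "detection of a minimum clinical difference of 3 points on the Likert scale between the 2 study groups". Its other inputs are 80% power, a 5% alpha and an SD of 7, and it ends with "2 × 7.8 × 5.4 = 90 per group". Allocation is 1:1 (Randomization and blinding), so the total is 180.

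**Recruitment target.** The Duration section writes "Given a sample size requirement of 90 patients and allowing for a 50% refusal/dropout rate" and concludes that about a year and a half will be enough. The Trial status section reports 36 patients recruited and adds: "The recruitment is expected to continue until the target sample size is reached". It gives no number for that target.

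**End of study.** The Duration section says: "The study will be terminated as soon as recruitment is complete". It adds 3 months for analysis and writing, and provides for an extension if recruitment is unfinished at a year and a half.

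**Follow-up.** Under Patient follow-up, patients are followed "until 4 months after the procedure or death whichever comes first", with telephone contacts scheduled to day 120. The primary outcome is measured at day 30. Secondary outcomes include pain and narcotic use at day 120, and survival.

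**The concern.** Two statements in the Duration section do not agree with the rest of the protocol.

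First, the number that tells staff when to stop enrolling appears as 90 per group in one section, as 90 patients in another, and without a figure in a third. With 36 patients recruited, either 90 − 36 = 54 or 180 − 36 = 144 remain. If enrolment stopped at the smaller figure, no later analysis could recover the lost precision.

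Second, a study that ends when the last patient is enrolled cannot also follow that patient for 4 months. Applied literally, the rule would cost the latest enrolees their day-120 data, and the very latest their primary outcome. The 3 months set aside afterwards are shorter than one patient's follow-up and are assigned to other work.

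**Working it through.** **1. The plan's own sample size.** The inputs are a difference of 3, an SD of 7, alpha 5% and power 80% (Sample size calculations). The tests are two-sided (Statistical analysis: "All *p*-values are two-tailed, and values < 0.05 will be considered statistically significant"), and 7.8 is the two-sided 5%/80% constant.
- Printed product: 2 × 7.8 × 5.4 = 84.2. With the unrounded ratio, 2 × 7.8 × (7/3)² = 84.9.
- The exact normal formula gives 86 per group and the t-based formula 87.

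The printed 90 is therefore not reproduced. It errs on the safe side, and this is a separate matter. Here 90 per group is taken as the stated requirement: 2 × 90 = 180.

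**2. Which total the timeline fits.** The Duration section gives 270 inoperable patients with pain a year and a 50% refusal/dropout allowance.
- Yield: 270 × 0.5 = 135 a year.
- 90 patients: 90/135 × 12 = 8 months.
- 180 patients: 180/135 × 12 = 16 months.
- Yield in 18 months: 1.5 × 135 = 202.5, enough for 180 and more than twice 90.

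The quoted year and a half fits 180 and not 90.

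**3. Power if 90 were taken as the total.** Power = Φ(δ / (σ√(2/n)) − 1.96), with δ = 3 and σ = 7.
- n = 90 per arm: 3 / (7 × 0.1491) = 2.875; Φ(0.915) = 0.82 (t-test 0.816).
- n = 45 per arm: 3 / (7 × 0.2108) = 2.033; Φ(0.073) = 0.53 (t-test 0.520).
- Difference detectable with 80% power at 45 per arm: 7 × (1.96 + 0.842) × √(2/45) = 4.1 points, against the planned 3.

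**4. Follow-up lost if the study ended at last enrolment.** This assumes 180 patients accrued evenly over 18 months (18 × 30.4 = 547 days).
- Day 120 not reached: 120/547 = 22%; 180 × 0.219 ≈ 40 patients.
- Day 30 not reached: 30/547 = 5%; 180 × 0.055 ≈ 10 patients.

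Deaths before the scheduled contact are ignored because the protocol gives no rate for them, so these counts are upper figures under even accrual.

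**5. The calendar.** The protocol allows 18 + 3 = 21 months.
- Recruitment finished at month 18: last day-120 contact at about 18 + 4 = month 22, after the planned end.
- Recruitment finished at month 16: last contact at about month 20, leaving about 1 month for analysis and writing.
- Break-even: 21 − 4 = about month 17.

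**The case against.** The strongest reply is that the intended meaning can be recovered. The section that derives the sample size says per group, the Duration section never says that 90 is a total, and its timeline matches 180. The Trial status target can be read as pointing back to the derivation. This stands: the protocol does not set the target at 90 in total, and a reader who inferred that the trial plans to halve its sample would go beyond the text. What remains is that 180 appears nowhere, and nobody should have to work back from an accrual rate to learn a trial's total.

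On the study end, the sentence about termination is followed by one about extending recruitment, so it may only mean that enrolment closes. Patient follow-up is stated without exception. That reading is fair, but the sentence speaks of the study and no other end is defined. A reader might infer that the 4-month follow-up is cut off as a whole; even on the literal reading, only late enrolees are affected. Nor does the last day-120 contact necessarily fall after the planned finish. It does so only if recruitment runs past about 17 months, which the extension sentence allows for.

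The power loss depends on the SD of 7. Scores on the 0–6 scale cannot have an SD much above 3, and changes on it (−6 to +6) cannot have one much above 6. For a 3-point difference, 45 per arm gives 99.7% power at SD 3, about 94% at SD 4 and about 80% at SD 5. This objection stands too: 52–53% is the consequence on the protocol's own inputs, not a forecast of the power the trial would actually have.

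**Conclusion.** The point holds as two internal contradictions that need correcting.

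- **Target.** The Duration section's 90 is half the 180 that the calculation implies. It is most likely a dropped 'per group'. If 90 were followed as a total, power on the stated inputs would fall from about 82% to 52–53%. That size is conditional on the SD of 7, which the scale makes implausible; with a smaller SD the loss is smaller.
- **Study end.** The termination rule conflicts with the follow-up section. Read literally, and assuming even accrual of 180 over 18 months, it would remove day-120 data for about 40 patients (22%) and the day-30 primary outcome for about 10 (5%).

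The documents do not show that the investigators intend to stop at 90 or to abandon follow-up.

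**What to change.** 1. In the Duration section, give the requirement as 180 patients (90 per group), and put the same number on the target in the Trial status section.
2. Replace the termination sentence with: *Enrolment closes when 180 patients are randomised; the study ends at the day-120 contact or death of the last randomised patient.*
3. Allow at least 4 months plus analysis time after recruitment, in place of the present 3 months.

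Reconciling the sections does not require a new rule for when the primary analysis is run.

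The cost is an amendment to wording and a stated calendar up to about 4 months longer. No patients are needed beyond the 90 per group already planned. The target should be settled before enrolment approaches 90.

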### Randomization and blinding

Participants will be randomized in 1:1 fashion, by sealed opaque envelopes, prepared by an independent third party, using a list produced by the web-based randomization service Sealed Envelope™.

Since the final inclusion criteria (accessibility of the celiac axis by EUS) is determined during the procedure, while the patient is sedated, the patient will be blinded to the treatment arm.

The research nurse who collects the data will not be present during the randomization process, nor the procedure, and will therefore also be blinded to the treatment arm.

### Study arms

EUS-CPN with bupivacaine: endoscopic ultrasound-guided bilateral celiac plexus neurolysis with absolute alcohol 20 mL preceded by injection of 10 ml of bupivacaine 0.5%EUS-CPN: endoscopic ultrasound guided bilateral celiac plexus neurolysis with absolute alcohol 20 mL only

### Patient follow-up

Patients will be followed in the immediate post-procedural period until 4 months after the procedure or death whichever comes first; see Fig. 1.

**Fig. 1 Fig1:**
[figure not shown]
Schedule of enrolment interventions and assessments

Immediate post-procedural surveillance:Likert pain scores pre-procedure (T0) and 30 min after arriving in recovery (T30) and then every 30 min until dischargeOpioid use in the last 3 days before the procedureVital signs pre-procedure (T0), immediately before and after neurolysis, and at 30 min after arriving in recovery (T30), and then every 30 min until dischargeRequirements for analgesia during the recovery period

Post-discharge surveillance:

Telephone interviews by a single research assistant on days 3, 7, 30, 60, 90, and 120* for:7-point Likert scale for pain (Table 2)Global rating scale of change (GRSC) (Table 2)Any adverse events (diarrhea, fever, dizziness, leg weakness)Hospital visitsNarcotic use.

**Table 2 Tab2:** Likert pain scale and GRSC

**7-point Likert scale for pain**	0 No discomfort at all 1 Minor discomfort 2 Mild discomfort 3 Moderate discomfort 4 Moderately severe discomfort 5 Severe discomfort 6 Very severe discomfort
**Global rating scale of change (GRSC)**	0 No improvement at all 1 Minor improvement 2 Mild improvement 3 Moderate amount of improvement 4 Quite a bit of improvement 5 A lot of improvement 6 Great improvement

*Days 3 and 7: ± 2 days; days 30, 60, 90, and 120: ± 4 days

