## Methods

### Objectives and design

The primary hypothesis for this study is that bupivacaine injection before neurolysis dilutes the neurolytic effect of alcohol and therefore decreases its analgesic effectiveness. We also believe that bupivacaine injection has no influence on intra- or immediate post-procedural pain.

The primary aim of study is to compare the effectiveness of EUS-CPN with and without bupivacaine. Secondary aims include a comparison of intra- and post-procedural pain, narcotic use, adverse events, and survival between the studied groups.

This is a single-center, randomized, double-blinded, parallel groups, non-inferiority clinical trial to be performed at the endoscopy unit of the Centre Hospitalier de l’Université de Montréal (CHUM) in Québec, Canada.

The SPIRIT reporting guidelines have been used in protocol formulation [9].

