### Secondary outcomes

% Difference in 7-point Likert scale and GRSC (Table 2):T0 and all other time points specified aboveTime to discharge from the endoscopy unit% Change in cumulative narcotic use for the previous 3-day period:T0 vs T60 daysT0 vs T120 daysRate of all intervention-specific adverse events (Using the American Society of Gastrointestinal Endoscopy classification) [10]Survival

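### Recovery pain scores stop at discharge but all count in a secondary outcome, so comparisons between arms after the 30-minute score rest on a subset formed after randomisation

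*Protocol article*

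**What the plan says.** Under Patient follow-up (the text with Fig. 1), immediate surveillance consists of "Likert pain scores pre-procedure (T0) and 30 min after arriving in recovery (T30) and then every 30 min until" discharge. The next pain score comes after the patient has left: "Telephone interviews by a single research assistant on days 3, 7, 30, 60, 90, and 120". No score is scheduled between discharge and the day-3 call.

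Under Secondary outcomes, the first entry is the percentage "Difference in 7-point Likert scale and GRSC (Table 2):T0 and all other time points specified" in the preceding text, which takes in the recovery readings. The same list has time to discharge from the endoscopy unit as a separate outcome.

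Under Objectives and design, the purpose of these scores is stated: "Secondary aims include a comparison of intra- and post-procedural pain, narcotic use, adverse events, and survival between the studied groups". The expectation is stated there too: "We also believe that bupivacaine injection has no influence on intra- or immediate post-procedural pain".

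Under Statistical analysis, "the paired Wilcoxon ranked sum test will assess the pain scores", with two-tailed p-values below 0.05 taken as significant.

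**The concern.** A patient who goes home after the 30-minute score has no 60- or 90-minute score. None was ever scheduled, so no later analysis document can recover it. From 60 minutes on, each arm is represented by the patients who have not yet left. Randomisation balances the arms at entry; it does not balance the groups still in the recovery room an hour later, because how long a patient stays may depend on the treatment. By listing time to discharge as an outcome, the protocol itself treats length of stay as something on which the arms may differ.

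Two things are at stake. The later comparisons lose sample size whatever drives discharge. If patients with less pain also tend to leave sooner, the arm with less pain loses more of its low scorers and the observed difference shrinks. The investigators expect no difference in immediate pain, so a late comparison that is null because of selection could be read as support for that expectation.

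**Working it through.** **The plan's own figures.** The article gives no figure for recovery pain and no discharge rates. The only sample size is for the day-30 outcome, stated as 90 per group. (Its printed product, 2 × 7.8 × 5.4, is 84.2; that is a separate matter and does not bear on this point.) I take the stated 90 per group below.

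**Who has a score at each time.**
- Pre-procedure and 30 minutes: scheduled for every patient.
- 60 minutes and later in recovery: only patients not yet discharged.
- Day 3 onwards: all patients in follow-up, by telephone.

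The selection is therefore confined to recovery scores after 30 minutes. A paired test does not remove it, because a patient without the later score contributes no pair.

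**Illustration of size.** All inputs except the 0–6 scale and the 90 per group are assumptions:
- latent pain is normal with means 2 and 3 and SD 1.6, stable over recovery;
- each reading adds measurement error of SD 0.7 and is rounded and clipped to 0–6;
- discharge is decided after the 30-minute score.

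In all patients the difference on the 0–6 scale is 0.90, with SDs of 1.57 and 1.65.

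Three kinds of discharge were simulated, with 2,000,000 patients per arm:
- *unrelated to pain*: about 40% leave at random;
- *graded*: log-odds of leaving = −0.4 − s × (score − 2.5), with s = 0.25 (weak), 0.5 (moderate) and 1.0 (strong);
- *hard cut-off*: everyone at or below a given 30-minute score leaves and everyone above it stays.

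| Discharge after the 30-minute score | Remaining at 60 min (lower-pain / higher-pain arm) | Difference among those remaining |
|---|---|---|
| Unrelated to pain | 60% / 60% | 0.90 |
| Graded, weak | 57% / 62% | 0.90 |
| Graded, moderate | 54% / 64% | 0.85 |
| Graded, strong | 49% / 64% | 0.73 |
| Hard cut-off, scores 0–1 leave | 61% / 81% | 0.56 |
| Hard cut-off, scores 0–2 leave | 39% / 61% | 0.44 |

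**Power** (normal approximation, two-sided 0.05): SE = √(SD₁²/n₁ + SD₂²/n₂), and power ≈ Φ(difference/SE − 1.96).
- All patients, 90 per arm: SE = √((1.57² + 1.65²)/90) = 0.24. Then 0.90/0.24 = 3.75 and power is about 96%.
- Discharge unrelated to pain, 54 per arm: SE = √((1.57² + 1.65²)/54) = 0.31. Then 0.90/0.31 = 2.90 and power is about 83%. This is loss of precision alone.
- Hard cut-off with scores 0–2 leaving, about 35 and 55 remaining with SDs 1.24 and 1.28: SE = √(1.24²/35 + 1.28²/55) = 0.27. Then 0.44/0.27 = 1.63 and power is about 36%.

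**No true difference.** With equal arms and the same discharge rule in both, the difference among those remaining is 0.00 in every setting.

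**A separate simulation over a longer stay**, with graded discharge repeated every 30 minutes, gives the same pattern. A true difference of 0.94 stays at 0.93 at 120 minutes with no dependence and falls to 0.78 at 60 minutes and 0.58 at 120 minutes with strong dependence.

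**The case against.** The strongest reply is that no discharge criterion appears anywhere in the article. Discharge could follow recovery from sedation or a fixed observation time, and then the difference is not distorted. A reader might infer that the arm with less pain necessarily loses its best patients and that the later comparisons are biased towards the investigators' belief. The documents do not support that as fact. It holds only if discharge depends on pain and a true difference exists. The hard cut-off figures are near the worst case; graded dependence gives much milder attenuation. This part of the objection stands.

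Second, the outcome wording covers the Likert scale and the GRSC together, and the GRSC is listed only for the telephone interviews. The text may not intend a separate test at each recovery reading. That is arguable, but the wording covers all the time points given, the recovery readings are among them, and post-procedural pain is a stated aim. The reading that includes them is the natural one.

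Third, a real effect on recovery pain could show elsewhere: in the 30-minute score, in analgesia required during recovery, and in time to discharge. This is correct and limits the harm, but it does not repair the comparisons at later times.

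Fourth, rules for missing scores are normally left to an analysis plan, which is not shown. Their absence is not the complaint. The article itself fixes both a schedule that ends at discharge and an outcome that uses every scheduled score.

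**Conclusion.** The structural point holds. As written, the plan includes between-arm comparisons after the 30-minute score among patients selected after randomisation. The certain cost is a shrinking sample. Bias is conditional: it needs discharge to depend on pain, which the documents neither state nor exclude, and it needs a real difference to attenuate. Under the assumed inputs, a true difference of 0.90 points appears at 60 minutes as anything from 0.90 to 0.44, the low end requiring a deterministic cut-off for which the documents give no basis.

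It should not be inferred that the trial's main result is touched. The 30-minute score, all telephone scores and the day-30 primary outcome do not depend on who remains in recovery. Severity is minor: the issue concerns the later readings within one secondary outcome, and it is cheap to correct.

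**What to change.** In Secondary outcomes, name the 30-minute recovery score, compared between arms with adjustment for the pre-procedure score, as the comparison of immediate post-procedural pain. Report the later recovery scores descriptively per arm, with the number of patients remaining at each time, alongside time to discharge and analgesia required in recovery.

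If one summary over the whole stay is wanted, use the last score before discharge, which exists for every patient with a 30-minute score. It is better than the worst score, which rises with length of stay because a longer stay gives more chances of a high reading. In the illustration with scores 0–2 leaving, the last score gives a difference of 0.90 and the worst score about 0.97, against 0.90 in all patients. The last score is taken at different times in different patients, so it should be read together with time to discharge.

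The cost is outcome wording only. The scores are already collected, and no visit, treatment or discharge practice changes. The downside is that the later recovery time points lose their separate tests.

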## Outcomes

### Primary outcome

Comparative change in Likert pain scores before procedure (T0) and at 30 days after the procedure (Table 2) with treatment failure defined as less than 3-point decrease in Likert pain scores.

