### Study population

All patients referred for EUS for suspected pancreatic malignancy or for neurolysis for pain due to proven pancreatic malignancy are eligible. The study will be presented to them by a single research assistant, who will also obtain study consent before the procedure. Patients will be randomized if they meet all inclusion criteria and have no exclusion criteria presented in Table 1.

**Table 1 Tab1:** Inclusion and exclusion criteria for the study

**Inclusion criteria**	1. Malignant-appearing pancreatic mass, or proven pancreatic cancer involving the pancreatic genu, body, or tail on imaging done before the endosonography 2. Any level of abdominal or back pain considered to be potentially related to the mass: a. New onset pain (< 3 months) b. Constant c. Centrally located d. With or without irradiation to the back e. No obvious other source of pain 3. No possibility of immediate surgical management. (Based on EUS evidence of venous involvement ≤ 1 cm from portal confluence and/or arterial involvement of the celiac axis or the splenic artery ≤ 1 cm from the bifurcation of the celiac axis, and/or evidence of liver metastases) 4. Signed, informed consent 5. Celiac axis accessible for *bilateral* neurolysis at EUS
**Exclusion criteria**	1. Allergy to bupivacaine 2. Tumors amenable for curative resection 3. Significant coagulopathy (platelets < 50000 µ/L, INR > 1.4, uninterrupted use of oral anticoagulants at therapeutic dosage [except for antiplatelet agents] 4. Patients with concurrent sepsis 5. Previous EUS CPN

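### The 3-point failure rule cannot be met by patients who enter with a pain score of 1 or 2, and the primary outcome does not say whether this rule or the score change is primary

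*Protocol article*

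**What the plan says.** All references are to the protocol article.

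- **Primary outcome** opens with a score comparison, "Comparative change in Likert pain scores before procedure (T0) and at 30 days after the procedure", and the same sentence continues with "treatment failure defined as less than 3-point decrease in Likert pain scores".
- **Table 2** defines the scale. Its lower end reads "0 No discomfort at all 1 Minor discomfort 2 Mild discomfort 3 Moderate discomfort" and its upper end "5 Severe discomfort 6 Very severe discomfort".
- **Table 1**, inclusion criterion 2, admits "Any level of abdominal or back pain considered to be potentially related to the mass". No inclusion or exclusion criterion sets a minimum score.
- **Sample size calculations** ties the size to the primary outcome and uses a "minimum clinical difference of 3 points on the Likert scale between the 2 study groups". Its other inputs are 80% power, a type I error of 5% and an SD of 7 points. It gives no failure rate and no difference in proportions.
- **Statistical analysis** lists a Wilcoxon test for pain scores, a t test for means, Fisher's exact method for proportions, and a later logistic model for predictors of a better pain outcome. It does not say which test is the primary one. P-values "are two-tailed, and values < 0.05 will be considered statistically significant".

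**The concern.** The scale, the entry rule and the failure rule are all printed, and together they do not work for part of the population that may be enrolled. At baseline 1 or 2 the floor of the scale lies closer than 3 points, so a complete responder is recorded as a treatment failure. At the other end, a patient who goes from 6 to 3 and still has moderate discomfort is a success.

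Forced failures do not depend on treatment. Randomization spreads them over both arms in expectation, so they shrink the difference in failure rates without carrying information about bupivacaine. They also affect the planned logistic model. If that model uses the failure variable, every patient with baseline 1 or 2 has the same outcome, and anything that goes with low baseline pain will look like a predictor of poor response.

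How much this matters depends on a second point that the sentence leaves open. It joins a continuous change and a binary failure and does not say which decides the trial. The figure of 3 points also serves twice, as a within-patient threshold and as a between-group difference in the sample size, and these are different quantities.

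**Working it through.** **The plan's own figure.** The printed formula gives 2 × 7.8 × (7/3)² = 84.9, or 84.2 with the rounded 5.4, where the article states 90 per group. The stated 90 is not reproduced. Nothing below depends on that gap; 90 per arm is used as stated. The formula is for a difference in means, so the plan contains no power figure for the failure rate.

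**Step 1: what the rule allows.** The largest possible fall equals the baseline score, because the floor is 0. Success needs a fall of at least 3.

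| Baseline (T0) | Largest fall | Day-30 score needed for success |
|---|---|---|
| 1 | 1 | impossible |
| 2 | 2 | impossible |
| 3 | 3 | 0 |
| 4 | 4 | 1 or less |
| 5 | 5 | 2 or less |
| 6 | 6 | 3 or less |

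This step uses only the article's own text.

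**Step 2: illustration of the effect on a failure-rate comparison.** The following inputs are assumptions, because the article gives neither a baseline distribution nor expected success rates:

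- f, the share with T0 of 2 or less: 0, 10, 20 or 30%, the same in both arms.
- True success among patients with T0 of 3 or more: 70% vs 50%.
- All 90 patients per arm assessed at day 30.

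The observed success rate is (1 − f) × true rate, so the observed difference is (1 − f) × 20 points. Power is the exact probability that Fisher's two-sided test gives p < 0.05, summed over all possible pairs of counts. The restricted analysis keeps the true rates but has only 90 × (1 − f) patients per arm.

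| f | Observed success, all patients | Difference | Power, all 90 per arm | Patients per arm with T0 ≥ 3 | Power, T0 ≥ 3 only | Gap |
|---|---|---|---|---|---|---|
| 0 | 70% vs 50% | 20 | 74.9% | 90 | 74.9% | 0 |
| 10% | 63% vs 45% | 18 | 61.5% | 81 | 68.6% | 7.1 |
| 20% | 56% vs 40% | 16 | 50.1% | 72 | 63.3% | 13.2 |
| 30% | 49% vs 35% | 14 | 42.2% | 63 | 58.4% | 16.2 |

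**Step 3: how much of the loss is due to forced failures.** The total loss from 74.9% is 13.4, 24.8 and 32.7 points at f = 10, 20 and 30%. The gap is 7.1/13.4 = 53%, 13.2/24.8 = 53% and 16.2/32.7 = 50% of that. The rest is the cost of having fewer patients who can respond by 3 points, and restricting the analysis does not recover it.

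**Step 4: sensitivity to the assumed rates.** With true success of 50% vs 30%, power with all 90 per arm is 66.8, 57.8 and 49.4% at f = 10, 20 and 30%. The restricted power is the same as in the table, since 50% vs 30% success mirrors 50% vs 70% failure. The gaps are then 68.6 − 66.8 = 1.8, 63.3 − 57.8 = 5.5 and 58.4 − 49.4 = 9.0 points. The direction holds, but the size depends on the assumption.

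**The case against.** The strongest reply is that the primary outcome is continuous. The sentence begins with a change in scores, the sample size is said to relate to the primary outcome and uses a points difference with a standard deviation, and a rank test is assigned to pain scores. On that reading failure is a subsidiary responder label, and a patient going from 2 to 0 counts as a 2-point improvement. This largely stands. It limits the reach of the point, but the failure rule is still part of the primary outcome sentence and still misclassifies complete responders wherever it is used.

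The second reply is that few patients may be affected. Eligible patients have constant pain, and some are referred specifically for neurolysis. This also stands: if the share with baseline 1 or 2 is near zero, so is the harm.

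A reader might go further and infer three things that the article does not support:

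- **That the primary analysis is invalid.** This would require failure to be the primary test, and the article does not say that it is.
- **That the whole fall in power from 75% to 42% is caused by the failure rule.** Step 3 shows that about half remains when the forced failures are excluded, and Step 4 shows that the rule's share can be smaller still.
- **That the rule tilts the trial towards a finding of non-inferiority.** The design carries that label under Objectives and design, and dilution does pull the arms together. But the article states no margin and plans two-sided tests at 0.05, so any such tilt cannot be measured and depends mainly on the missing margin, which is a separate matter.

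**Conclusion.** The inconsistency is certain: three stated elements make success impossible at baseline 1 or 2 and possible at baseline 3 only with complete relief. Its consequence is conditional. It applies in full only if the failure rate is the primary comparison, and its size depends on a baseline distribution that the article does not give. Under the assumed 70% vs 50% success, forced failures cost about 7, 13 and 16 points of power when 10, 20 and 30% of patients start at 2 or below. Under 50% vs 30% they cost about 2, 5 to 6, and 9 points. These figures illustrate the mechanism and are not estimates for this trial. The point should be fixed because it sits in the primary outcome and is cheap to settle, but it is not a fatal defect.

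**What to change.** Name one primary outcome: the between-group comparison of the day-30 Likert pain score, adjusted for T0. It is on the same scale as the sample size, although that calculation assumed an unadjusted difference. Adjustment is a refinement in the analysis and needs no new data.

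Keep failure, with its present 3-point threshold, as a secondary outcome. Analyse it in patients with T0 of 3 or more, and include T0 in the logistic model. T0 is measured before the procedure and so before allocation, which means that the restriction does not break the randomized comparison. A failure definition attainable at every enrolled baseline would also remove the contradiction, but the article would still have to say which outcome is primary.

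The cost is a change of protocol wording, with the registry entry brought into line, submitted to the ethics board and settled before unblinding. The article reports 36 patients recruited at the time of writing. Eligibility, treatment and data collection stay as they are. The downside is a smaller denominator for the secondary failure rate, for example 72 instead of 90 per arm if 20% start at 2 or below.
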